### Survey data

Demographic information, current exercise behaviours (APSS), scores of depression, anxiety and stress (DASS-21), health-related quality of life (EHP-30), sleep (PSQI), self-efficacy (SEE) and open-ended questions regarding treatment, geographical location, fertility and access to care, will be collected pre- and post-intervention. Moreover, symptoms will be tracked weekly via the Endometriosis Impact Scale (EIS) through REDCap, a survey administration software program.

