## Data analysis

All data will be de-identified for analysis and reporting. The estimated sample size was determined using data from Gonçalves et al.[25] where the mean difference for pain between the control and intervention was 24.74, for an effect size of d = 1.33 and comparisons between four groups, a sample size of 32 was estimated (alpha at 0.05 and power 0.80). Factoring in attrition and funding availability, the target sample size was set to 50. However, a piecewise (segmented) mixed-effect regression will be used to determine the critical threshold for exercise dose (primary outcome). Exercise dose (all randomized participants) will be determined by duration and intensity (heart rate) variables, aggregated weekly. For a sample of 50 participants across 12 weeks, with a mixed-effects piecewise model, there will be a minimum of 600 observations, which provide sufficient power and stability for this type of analysis[26]. Threshold and detectable change in slope will be determined by Y^t^ = B^0^ + B^1^* time^t^ + b^2^ * intervention^t^ + b^3^ time after intervention^t^ + e^t^, and confirmed with Davies Test. Intercurrent events such as medication changes, clinical exacerbations and poor adherence will be time- and date-stamped for consideration as co-variates in the regression analysis.

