All other data will be reported as mean ± standard deviation (SD) or median interquartile ranges. Normal distribution will be determined by Shapiro-Wilk’s test and non-normally distributed data will be logarithmically transformed prior to analysis. Pain, as a subset of the EHP-30 is the primary endpoint and will be analysed with an intention-to-treat analysis. A sensitivity (per-protocol analysis) will also be conducted to confirm outcomes. Secondary and exploratory endpoints will be arranged hierarchically as follows; quality of life (EHP-30), depression, stress, anxiety (DASS-21), functional capacity, sleep (PSQI), estradiol, CRP, cortisol. Multiple comparisons will be adjusted for using the Benjamini-Hochberg false discovery rate procedure. Missing data will be managed depending upon the volume of data, complete case analysis will be performed (<5%) for 5–40%, multiple imputation for chained equations or random forest imputation will be employed. Complier average causal effect (CACE) analysis will be employed if compliance varies significantly. Significance will be set at p < 0.05. All statistical procedures will be performed using Statistical Package for the Social Sciences (SPSS; Windows version 31.0, Chicago, IL, USA) and R Studio (2026.07.1).

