## Limitations

This study is not without limitations. To address the spatial factors affecting endometriosis care, the mode of delivery is telehealth, as such this presents limitations with monitoring, adherence and attrition. As the exercise prescription is self-directed, adherence may be low, and attrition may result, and this may then reduce the power and observations. Moreover, the use of the activity monitor may vary depending upon user (logging physical activity), and therefore, some data may not be as reliable as laboratory-based data. Further, biomarker sampling, conducted via self-collected dried blood spots, was random and therefore not aligned with the menstrual cycle. Accordingly, data may not be indicative of maximal inflammatory and hormonal load associated with the condition and should be interpreted with caution. Finally, this study upheld strict exclusion criteria, so findings may not be applicable to individuals who present with comorbidities such as adenomyosis. To counter these limitations, future studies should consider fully supervised and individualized interventions.

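### The volume-based imputation rule does not exempt the weekly EIS scores; chained equations without the breakpoint would shrink the slope change that the threshold analysis looks for, and imputing this outcome is unnecessary

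*Protocol article*

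**What the plan says.** The Data analysis section sets out the threshold analysis first: "a piecewise (segmented) mixed-effect regression will be used to determine the critical threshold for exercise dose (primary outcome"). Its exposure is weekly: "Exercise dose (all randomized participants) will be determined by duration and intensity (heart rate) variables, aggregated weekly". The section does not name the outcome of this model, but the EIS is the only symptom score collected every week (Survey data: "symptoms will be tracked weekly via the Endometriosis Impact Scale (EIS) through REDCap"). The size of the series is given as "For a sample of 50 participants across 12 weeks, with a mixed-effects piecewise model, there will be a minimum of 600 observations". No missing-data rule is attached to this model.

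The section then turns to the remaining analyses with "All other data will be reported as mean ± standard deviation (SD) or median interquartile ranges". After the endpoint hierarchy and the multiplicity adjustment comes one missing-data rule, which begins "Missing data will be managed depending upon the volume of data, complete case analysis will be performed (<5%) for 5–40" (the upper band, in per cent missing). The method stated for that upper band is "multiple imputation for chained equations or random forest imputation will be employed". The rule depends only on the percentage missing. It names no variables and exempts none, and it does not say what the imputation model contains.

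Under Limitations the authors expect losses in a self-directed programme: "adherence may be low, and attrition may result, and this may then reduce the power and observations". They give no rate.

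**The concern.** An imputation model should contain every feature of the relation that the analysis model will estimate. Here the analysis looks for a change in slope. If missing weekly scores are drawn from a model that relates symptoms to dose by a straight line, the imputed weeks carry no bend. Once they are pooled with the observed weeks, the fitted slope change is pulled towards zero. More imputations or correct pooling do not help, because the error lies in the model that generates the imputed values.

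What is at stake is the trial's central question. The bias runs towards finding no threshold and grows with the amount of missing data. The step also gains little. A mixed model fitted by likelihood uses each woman's observed weeks and needs no imputed outcomes when data are missing at random.

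**Working it through.** **Size of the band.** 50 women × 12 weeks = 600 weekly records, which reproduces the article's figure. The imputation band is then 0.05 × 600 = 30 to 0.40 × 600 = 240 records.

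**Rough expectation.** Suppose a share *p* of the weeks is imputed without any bend. The recovered slope change should be near (1 − *p*) × 1 + *p* × 0 = 1 − *p*, that is 0.95 at 5% missing, 0.80 at 20% and 0.60 at 40%.

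**Simulation 1.** Inputs from the article: 50 women, 12 weeks, and weekly dose built from the arm prescriptions under Exercise intervention. Assumptions not in the article: slope change −0.10 per minute at 80 minutes, between-woman SD 8, residual SD 6, outcome missing completely at random, dose fully observed. There were 60 replicates per rate with 5 imputations each. The slope change was read at the true breakpoint from a random-intercept GLS fit. Entries are the mean estimate divided by the true slope change; the Monte Carlo standard error is about 0.03 to 0.06.

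| Handling of missing weekly outcome | 5% | 20% | 40% |
|---|---|---|---|
| Mixed model on observed weeks, no imputation | 0.99 | 1.03 | 1.01 |
| Linear imputation, no person term, no breakpoint | 0.95 | 0.82 | 0.64 |
| Linear imputation, person effects, no breakpoint | 0.94 | 0.81 | 0.63 |
| Imputation with person effects and breakpoint | 0.99 | 1.03 | 1.00 |
| Random forest, no person information | 0.99 | 1.01 | 1.05 |
| Random forest with the person mean | 0.97 | 0.91 | 0.77 |

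Three things follow.

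- Linear imputation without the breakpoint loses 1 − 0.95 = 5% at the bottom of the band and 1 − 0.64 = 36% at the top, close to the rough expectation.
- Adding person effects changes almost nothing (0.64 against 0.63 at 40%), while adding the breakpoint removes the loss. The omitted breakpoint is therefore the cause.
- Random forest gave no shrinkage in one set-up and 3% to 23% in the other.

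**Simulation 2, other assumptions.** Known breakpoint at 75 min/week with no effect below it, intraclass correlation 0.5, missing completely at random, 300 trials per rate with 10 imputations each. Linear imputation on dose and week recovered 0.86, 0.70 and 0.57 at 15%, 30% and 40% missing. Adding arm gave 0.92, 0.82 and 0.72. The mixed model on observed weeks gave 1.03, 1.01 and 0.98.

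**Simulation 3, other forms of chained equations.** Again with a known bend in dose and outcomes missing completely at random.

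| Form | 20% | 40% |
|---|---|---|
| Long format, linear | 0.81 | 0.63 |
| Long format, predictive mean matching | 0.90 | 0.75 |
| Wide by week | 0.81 | 0.51 |

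The mixed model on observed weeks recovered 1.00–1.02. Shrinkage is thus 1 − 0.90 = 10% to 1 − 0.81 = 19% at 20% missing, and 1 − 0.75 = 25% to 1 − 0.51 = 49% at 40%.

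**Location of the breakpoint.** In simulation 1 the breakpoint was also estimated by grid search. The mean lay between 79.8 and 87.6 minutes across all methods and rates (true value 80), with a standard deviation of roughly 15 to 26 over 60 replicates. No consistent shift due to imputation is visible. The demonstrated harm is to the size of the slope change.

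**The case against.** The strongest reply is that the article never says the rule reaches the weekly series. The rule follows a sentence about the other data and a list of endpoints that omits the EIS. The remark under Limitations that attrition would reduce the observations also fits a model run on observed records. This has some force: the scope is an inference. However, the reference to other data is the subject of the reporting sentence only. The missing-data sentence starts afresh and stands beside statements that plainly cover the whole trial, such as the significance level and the software. The narrower reading would also leave the analysis labelled primary outcome with no missing-data rule at all.

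Second, the article names families of methods, not a model. Chained equations can be multilevel and can include a breakpoint term, and such detail is commonly left to an analysis plan. This stands. A reader might infer that the plan commits itself to an imputation that flattens the bend, but the text does not fix that. What it does fix is a choice by percentage missing, without regard to the analysis model.

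Third, a reader might infer that random forest also ignores the breakpoint, or that the bias comes from ignoring repeated weeks. The simulations support neither.

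Fourth, the simulations place a known bend in dose, whereas the equation printed in Data analysis is segmented in time. The same reasoning would apply to any change in slope left out of the imputation model, but the time-segmented form was not simulated.

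Finally, likelihood deals with missing outcomes, not missing dose. Limitations mentions uneven use of the activity monitor, so dose may well have gaps. Imputation is unnecessary for the EIS, not necessarily for dose.

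**Conclusion.** The point holds in a conditional form and deserves a change of wording. On its natural reading, the rule sends 5–40% missing weekly EIS values to chained equations or random forest. If the method is chained equations without the breakpoint, the estimated slope change shrinks by about 5% at 5% missing, 10–20% at 20% and 25–50% at 40%. Fitting the observed weeks avoids this.

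These sizes assume a known bend in dose, outcomes missing completely at random and fully observed dose. Informative dropout and missing dose were not simulated. The article gives no missingness rate, so entry into the band is plausible but not established, and low adherence in itself means a low dose, not a missing score. The material does not support saying that the plan will flatten its threshold, that both named methods do so, or that the location of the threshold is shifted.

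**What to change.** Limit the volume-based imputation rule to the endpoints measured before and after the intervention. State that the segmented mixed model is fitted by maximum likelihood to all observed weekly EIS records, without imputing the EIS. If weekly dose has to be imputed, use a multilevel imputation model that contains the segmented term, so that it is compatible with the analysis model.

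For the EIS this is a change of a sentence or two and saves work. The only cost is some extra programming if weekly dose is imputed.

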## Ethics and dissemination

Participants will be required to provide written and verbal consent following an outline of all procedures. This study conforms to the Declaration of Helsinki and has institutional ethics and biosafety approvals. Findings will be shared through publication and presentation at industry conferences and through collaborations with endometriosis advocacy groups.

## Limitations

This study is not without limitations. To address the spatial factors affecting endometriosis care, the mode of delivery is telehealth, as such this presents limitations with monitoring, adherence and attrition. As the exercise prescription is self-directed, adherence may be low, and attrition may result, and this may then reduce the power and observations. Moreover, the use of the activity monitor may vary depending upon user (logging physical activity), and therefore, some data may not be as reliable as laboratory-based data. Further, biomarker sampling, conducted via self-collected dried blood spots, was random and therefore not aligned with the menstrual cycle. Accordingly, data may not be indicative of maximal inflammatory and hormonal load associated with the condition and should be interpreted with caution. Finally, this study upheld strict exclusion criteria, so findings may not be applicable to individuals who present with comorbidities such as adenomyosis. To counter these limitations, future studies should consider fully supervised and individualized interventions.

## Related research article

None.

## Data Availability

No data was used for the research described in the article.
